### Radiotherapy quality assurance

Efforts will be made to keep treatment interruptions to a minimum when feasible. Treatment interruptions are allowed when clinically required at the discretion of the treating physician, for example to allow for patient recovery after resection or between fractions of fractionated SRS or based on available treatment days given holiday schedules. Radiotherapy compliance criteria are listed in Table 4.

**Table 4 Tab4:** Radiotherapy compliance criteria

**1.0 Minor deviations**	1.1 < 95% but ≥90% of the prescribed dose completely encompasses the clinical target volume 1.2 > 3 weeks between resection and start of post-operative SRS in the standard arm 1.3 > 1 week between the end of pre-operative SRS and resection in the experimental arm
**2.0 Major deviations**	2.1 > 2 weeks between planning MRI and start of SRS 2.2 Prescribed dose is ≤90% dose required by the study 2.3 < 90% of the prescribed dose completely encompasses the clinical target volume 2.4 Maximum point dose to the optic chiasm is > 10 Gy for treatments delivered in one fraction, > 20 Gy for treatments delivered in three fractions, or > 25 Gy for treatments delivered in five fractions 2.5 Maximum point dose to the brainstem is > 15 Gy for treatments delivered in one fraction, > 3.1 Gy for treatments delivered in three fractions, or > 31 Gy for treatments delivered in five fractions 2.6 > 6 weeks between resection and start of post-operative SRS in the standard arm or > 3 weeks between the end of pre-operative SRS and resection in the experimental arm > 2 weeks to complete a course of fractionated SRS 2.8 Resection is not performed (or cancelled) for any reason

*Abbreviation*: *SRS* stereotactic radiosurgery

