### Radiotherapy

A linear accelerator (LINAC) using ≥4 megavoltage (MV) photons, with collimation using micro-multi-leaf collimators (5 mm width or less at isocenter) or cones, Gamma Knife or Cyberknife may be used to deliver SRS. All patients will be counselled about thermoplastic mask fixation, CT simulation and immobilization in detail. Localization, simulation, and immobilization will be as per institution standard.

For the tumor bed (standard arm only), the gross tumor volume (GTV) will consist of the tumor bed including residual tumor, if present, on T1-weighted MRI (with gadolinium contrast, unless contraindicated) or CT scan (with contrast, unless contraindicated). The clinical target volume (CTV) will be GTV plus 2 mm and can be cropped for natural barriers to spread (e.g., bone) or structures not at-risk for tumor infiltration. The planning target volume (PTV) will be the CTV plus 0 to 1 mm when using mask-based immobilization (no margin will be added when using frame-based immobilization). For intact metastases on both arms, the GTV will consist of all visible tumor on T1-weighted MRI or CT scan. No margin will be added for CTV. The PTV will be the CTV plus 1 mm when using mask-based immobilization (no margin will be added when using frame-based immobilization). Radiosurgery dose and fractionation is based on the NCCTG N107C/CEC.3 trial [7] with modification (Table 3). Treatment will be delivered on consecutive days, one fraction per day, for fractionated radiotherapy regimens.

**Table 3 Tab3:** Radiotherapy dose and fractionation

Tumor Bed (standard arm) (prescription is based on CTV volume)	Intact metastases (both arms) (prescription is based on the CTV maximal diameter)
Lesions < 4.2 cc receive 20 Gy	Lesions < 1.0 cm receive 22–24 Gy
Lesions ≥4.2 to < 14.4 cc receive 17 Gy	Lesions ≥1.0 to < 2.0 cm receive 20–22 Gy
Lesions ≥14.4 to < 30 cc receive 27 Gy in three or 30 Gy in 5 fractions	Lesions ≥2.0 to < 3.0 cm receive 18–20 Gy
Lesions ≥30 cc receive 24–27 Gy in 3 fractions or 30 Gy in five fractions	Lesions ≥3.0 to < 5.0 cm receive 27 Gy in 3 or 30 Gy in five fractions
	Lesions ≥5.0 cm receive 24–27 Gy in three fractions or 30 Gy in five fractions

The dose should be prescribed to the highest isodose line encompassing the CTV and be between the 50 and 90% of the maximum dose

*Abbreviation*: *CTV* clinical target volume

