Critical organs at risk (OAR) include the optic nerves and optic chiasm. A margin of 1 mm when using mask-based immobilization (no margin when using frame-based immobilization) will be added to each OAR to create each planning OAR volume (PRV). The dose constraints for the optic nerve and chiasm PRVs are Dmax ≤10 Gy in one fraction, ≤20 Gy in three fractions, and ≤ 25 Gy in five fractions; and for Brainstem are Dmax ≤15 Gy in one fraction, ≤23.1 Gy in three fractions, and ≤ 31 Gy in five fractions.

Multiple isocenter, non-isocentric, and non-coplanar beams may be used. Few parameters to be followed while planning and plan evaluation: 95% of the prescribed dose should completely encompass the target (CTV). Dose conformity (for CTV) should be between 1.0 and 2.0 for lesions ≥5 mm in maximum diameter (may be up to 3.0 for lesions < 5 mm in maximum diameter). The minimum and maximum CTV dose, conformity index (defined as the ratio of the prescription isodose volume to the target volume, i.e., CTV), prescription isodose line, maximum point dose to the optic nerves and chiasm, and dose received by 1 cc of the brainstem should be calculated and reported. The isodose distribution for each plan should be submitted in DICOM-RT format. Total PTV volume, normal brain (brain-GTV) volume receiving 12 Gy (V_12 Gy_) will also be recorded.

Patients may receive other medications/treatments as required. Only steroid therapy will be recorded in the case report forms. Cytotoxic chemotherapy should be stopped during SRS. Immunotherapy may be continued during SRS.

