### Statistical analysis

Two types of population will be analyzed:Intent-to-treat population: All patients will be analyzed in the groups to which they were randomized, regardless of whether they received or adhered to the allocated intervention.Per-protocol population: All patients who fulfil eligibility criteria, received, and adhered to treatment assigned, and completed required assessments. For example, patients who had their resection cancelled or not completed will not be analyzed in the per-protocol population analysis.

Interim analysis for futility and efficacy is planned. One interim analysis is planned when 44 events are seen (approximately 50% of total planned events). The interim analysis will be completed and submitted to the Data and Safety Monitoring Board (DSMB) within 60 days of reaching that event. The Pocock beta spending function is used for early stopping for futility and Lan-Demets O’Brien-Flemming alpha spending function is used for early stopping for efficacy.

Descriptive statistics will be used to report baseline characteristics. The mean and standard deviation will be used to describe normally distributed continuous variables; the median and interquartile range will be used to describe non-normally distributed continuous variables. The t-test will be used to compare the continuous variables and the χ2 test will be used to compare categorical variables between arms. Survival will be estimated using the Kaplan-Meier method and compared between arms with two-sided log-rank tests. Hazard ratios will be estimated using the Cox proportional-hazard models adjusted for baseline and stratification variables. Statistical significance will be based on a two-sided α of 0.05. Statistical analyses will be conducted using the current version of SAS at the time of analysis (SAS Institute, Cary, NC).

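### Table 4 makes a three-fraction brainstem maximum above 3.1 Gy a major deviation, although the planning constraint allows up to 23.1 Gy

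*Protocol article*

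**What the plan says.** The protocol article gives brainstem dose limits in two places.

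- **Planning constraint** (Methods, Radiotherapy): "for Brainstem are Dmax ≤15 Gy in one fraction, ≤23.1 Gy in three fractions, and ≤ 31 Gy in five fractions".
- **Major-deviation rule** (Radiotherapy quality assurance, Table 4 item 2.5): "Maximum point dose to the brainstem is > 15 Gy for treatments delivered in one fraction", then "> 3.1 Gy for treatments delivered in three fractions", then "> 31 Gy for treatments delivered in five fractions".

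The Radiotherapy section also constrains the optic nerves and chiasm, at "Dmax ≤10 Gy in one fraction, ≤20 Gy in three fractions, and ≤ 25 Gy in five fractions". Table 4 item 2.4 repeats those three doses as major-deviation thresholds for the chiasm.

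Three-fraction treatment is a real option in the trial. Table 3 allows it for tumor beds of 14.4 cc or more and for intact lesions of 3.0 cm or more; for the largest intact lesions it reads "Lesions ≥5.0 cm receive 24–27 Gy in three fractions or 30 Gy in five fractions".

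In the Statistical analysis section, the per-protocol population is limited to eligible patients who received and "adhered to treatment assigned, and completed required assessments".

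**The concern.** A planning limit and the deviation rule that enforces it should agree. For the brainstem in three fractions they differ by 20 Gy, for the same organ, the same measure (maximum dose) and the same number of fractions. Nothing else in the article reconciles them.

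Table 4 is the trial's list of radiotherapy compliance criteria, so this is a working threshold. A quality-assurance reviewer who applies it literally will record major deviations for plans that satisfy the protocol. A reviewer who quietly substitutes 23.1 Gy departs from the written rule. If centers or reviewers differ, deviation rates stop being comparable.

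There is also a possible route into the analysis. The one example given of exclusion from the per-protocol set, a resection that is cancelled or not completed, also appears in Table 4 as a major deviation (item 2.8). It would be natural, though the article does not say so, to use Table 4 to judge adherence in general. Wrongly graded patients could then drop out of that set.

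**Working it through.** **1. Each constraint against its deviation threshold.** Inputs are the dose limits in the Radiotherapy section and Table 4 items 2.4 and 2.5. Per-fraction dose is total dose divided by number of fractions.

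| Organ | Fractions | Constraint (Gy) | Major deviation above (Gy) | Per fraction: constraint / threshold (Gy) | Agree? |
|---|---|---|---|---|---|
| Optic | 1 | 10 | 10 | 10.00 / 10.00 | yes |
| Optic | 3 | 20 | 20 | 6.67 / 6.67 | yes |
| Optic | 5 | 25 | 25 | 5.00 / 5.00 | yes |
| Brainstem | 1 | 15 | 15 | 15.00 / 15.00 | yes |
| Brainstem | 3 | 23.1 | 3.1 | 7.70 / 1.03 | **no** |
| Brainstem | 5 | 31 | 31 | 6.20 / 6.20 | yes |

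Setting the threshold equal to the constraint reproduces five of the six entries. Only the three-fraction brainstem entry fails.

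**2. Which figure is wrong.** A total-dose limit should rise with the number of fractions, and the limit per fraction should fall.

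- With 23.1 Gy, the brainstem totals are 15, 23.1 and 31 Gy and the per-fraction values are 15.0, 7.7 and 6.2 Gy. Both sequences are in order.
- With 3.1 Gy, the totals are 15, 3.1 and 31 Gy and the per-fraction values are 15.0, 1.03 and 6.2 Gy. Neither is in order, and the three-fraction limit is 3.1/15 = 21% of the single-fraction limit.

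So 3.1 Gy is the faulty entry, and it differs from 23.1 by one leading digit.

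**3. What happens to a three-fraction plan as written.**

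- Maximum of 3.1 Gy or less: constraint met, no deviation.
- Maximum above 3.1 and up to 23.1 Gy: constraint met, **major deviation**.
- Maximum above 23.1 Gy: constraint broken, major deviation.

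The middle band is 23.1 − 3.1 = 20.0 Gy wide, or 20.0/23.1 = 86.6% of the permitted range. This is a share of the dose scale, not of plans or patients.

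**4. How low 3.1 Gy is against the prescriptions.** Table 3 gives 24 to 27 Gy in three fractions.

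- 3.1/27 = 11.5% and 3.1/24 = 12.9%
- 23.1/27 = 85.6% and 23.1/24 = 96.3%

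Low-dose spill of about an eighth of the prescription would be enough to trigger the rule as printed.

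**5. Possible weight in the per-protocol set.** The Sample size section plans 44 patients per arm. If adherence were judged on Table 4, each wrongly graded patient would remove 1/44 = 2.3% of a planned arm. The actual per-protocol arm may be smaller than 44, so this is only a guide.

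**The case against.** The strongest reply is that this is an obvious misprint with little consequence. The right value is stated in the Radiotherapy section, the sequence 15, 3.1, 31 looks wrong at a glance, and a careful reviewer would probably notice. The error only over-flags: every plan above 23.1 Gy is still caught, so no patient is exposed to more dose because of it. Nothing shows that any plan was graded against 3.1 Gy.

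The source is also uncertain. The article condenses protocol version 1.0, which is not available here. The same cell of Table 4 lacks the label 2.7 before the rule on completing a fractionated course, so a character may have been lost in typesetting or in text extraction, and the operational protocol may be correct.

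Finally, the article does not make a Table 4 deviation a ground for per-protocol exclusion, and three-fraction treatment always has a five-fraction alternative in Table 3, so the number of affected plans is unknown and could be small.

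All of this stands as a limit on the consequence. None of it removes the contradiction. The neighboring doses in the cell are intact, the threshold as printed is wrong, and a compliance table should not depend on readers spotting and overriding an entry.

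**Conclusion.** The point holds. As printed, Table 4 item 2.5 contradicts the three-fraction brainstem constraint by 20.0 Gy and grades compliant plans as major deviations across 87% of the permitted dose range. That 23.1 Gy is the intended figure is an inference, but a strong one: it restores agreement in all six entries and puts both brainstem sequences in order.

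The certain effect is on compliance grading. An effect on the per-protocol analysis requires that adherence be judged on Table 4, which is an assumption. The number of plans affected cannot be given, because the article has no count of three-fraction treatments or of targets near the brainstem. Planned treatment, the intent-to-treat analysis, power and significance level do not change. It should be fixed, but it does not threaten the trial's main result.

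**What to change.** 1. Check the three-fraction brainstem threshold in the full protocol (version 1.0) and in any quality-assurance checklist in use.
2. Correct Table 4 item 2.5 so that the three-fraction threshold is above 23.1 Gy. All six thresholds then equal their constraints, and no plan can meet the constraint and fail this item.
3. Send a short note to sites and quality-assurance reviewers, and re-grade any plan that was scored against 3.1 Gy.

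Optionally, add the brainstem maximum point dose to the list of reported plan values. The Radiotherapy section asks for the dose to 1 cc of brainstem, while both the constraint and the deviation rule use the maximum. This is not essential, since "The isodose distribution for each plan should be submitted in DICOM-RT format" already lets the maximum be assessed.

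The cost is one figure in one table and a note. Re-grading is needed only if the wrong figure was actually applied.

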### Reporting of adverse events and serious adverse events

This protocol does not contain investigational agents, and adverse events secondary to radiotherapy should be reported in the manner described in Table 5. Common Terminology Criteria for Adverse Events (CTCAE), version 5.0 will be used for adverse event reporting.

**Table 5 Tab5:** Adverse events reporting

Study Period/Reporting Procedure	Adverse Event Reporting	SAE Reporting
From time patient signs the consent form until 30 days after end of study treatment.	Yes	Yes
Thirty days after the end of study intervention until the last follow up date.	Yes, if assessed as related or possibly related to the treatment/intervention by the Investigator.	Yes, if assessed as related or possibly related to the treatment/intervention by the Investigator.
How to report	Source documents (e.g., study-specific worksheets) and case report form.	SAEs, unexpected, related/possibly related to be reported through a SAE form to the PI (sponsor) with copy to the Investigator-Initiated Trials team within 24 hours REB/Health Canada to be notified within applicable timeframe.

*Abbreviations*: *PI* principal investigator, *REB* research ethics board, *SAE* serious adverse event

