### Randomization and treatment allocation

Patients will be allocated by blocked randomization (block size of 16), on a 1:1 basis, to either the standard or investigational arm. Patients will be stratified according to the following factors: age (< 60 years versus ≥60 years), histology (melanoma/renal cell carcinoma/sarcoma versus other) and number of metastases (1 versus 2–10). A computer-generated list has been uploaded into the Electronic Data Capture (EDC) system for randomization. After confirming a participant’s eligibility, the study staff will randomize the patient using the EDC. Following randomization, treatment will be initiated within two weeks. Because of the difference in treatment sequencing (before or after surgery), blinding of trial participants or investigators will not be possible; neuropathologists and neuroradiologists will prospectively review applicable material without knowledge of the random assignment.

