### Interventions

The following procedures will be performed during the treatment phase of the trial:Standard arm: Resection of ≥1 brain metastases followed by postoperative tumor bed SRS within 3 weeks.Investigational arm: Preoperative SRS followed by resection of ≥1 brain metastases within 1 week.

Patients treated on both arms will receive primary SRS for unresected brain metastases.

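### Unconditional adverse event recording stops at a date that depends on the arm, and afterwards an unblinded investigator's attribution decides what is recorded

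*Protocol article*

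**What the plan says.** Under Reporting of adverse events and serious adverse events, Table 5 sets two periods. The first runs "From time patient signs the consent form until 30 days after end of study treatment", and both adverse events and serious adverse events are entered with no condition. The second runs "Thirty days after the end of study intervention until the last follow up date", and the entry becomes "Yes, if assessed as related or possibly related to the treatment/intervention by the Investigator".

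The sentence that introduces the table gives a narrower scope: "adverse events secondary to radiotherapy should be reported in the manner described in Table 5".

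The Interventions section fixes the order of treatment and the longest gap. The standard arm is "Resection of ≥1 brain metastases followed by postoperative tumor bed SRS within 3 weeks" and the investigational arm is "Preoperative SRS followed by resection of ≥1 brain metastases within 1 week". Table 4 calls the gap a major deviation only when it exceeds 6 weeks (standard) or 3 weeks (investigational).

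Randomization and treatment allocation states that "blinding of trial participants or investigators will not be possible". The same sentence provides for neuropathologists and neuroradiologists to review applicable material masked to arm. Table 6 schedules an adverse event review and an MRI at 3, 6, 9, 12, 16 and 24 months, counted from the last treatment date with a window of 2 weeks either way.

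**The concern.** The end of treatment is not the same point in the two arms. It comes after SRS in one and after surgery in the other, and the permitted gap before it differs threefold. A recording period tied to that date can give the arms different lengths of unconditional capture, and different lengths after each procedure. Once it closes, whether an event is recorded depends on a judgement by someone who knows the sequence used.

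Lower toxicity is part of the case for preoperative SRS. The Abstract lists adverse radiation events, including radiation necrosis, among the secondary endpoints. The Background cites retrospective necrosis rates at two years, far beyond a 30-day cut-off. The data and safety monitoring board also reviews reported adverse events every six months, so unequal recording could affect monitoring as well as the final comparison.

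**Working it through.** The plan gives no length for the recording window by arm, so there is no stated figure to reproduce. The window follows from the document's own limits.

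**Inputs**
- Randomisation to start of treatment: up to 14 days, both arms (Randomization and treatment allocation).
- Gap between procedures: up to 21 days standard, up to 7 days investigational (Interventions); major deviation beyond 42 and 21 days (Table 4).
- SRS course: one, three or five fractions on consecutive days (Radiotherapy), so a span of 0 to 4 days.
- Tail after end of treatment: 30 days (Table 5).

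**Day after randomisation on which unconditional recording stops, five fractions**
- Standard: 14 + 21 + 4 + 30 = day 69.
- Investigational: 14 + 4 + 7 + 30 = day 55.
- Difference: 69 − 55 = 14 days.
- At the major-deviation limits: 14 + 42 + 4 + 30 = day 90 v 14 + 4 + 21 + 30 = day 69, a difference of 21 days.

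**Sensitivity to the gap.** The documents give upper limits, not actual gaps. The gaps below are assumptions except for the first and last rows, which are the document's limits. Length from first treatment, single fraction, is gap + 30.

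| Gap, standard v investigational (days) | Standard | Investigational | Difference |
|---|---|---|---|
| 21 v 7 (permitted maxima) | 51 | 37 | +14 |
| 10.5 v 3.5 (half of each) | 40.5 | 33.5 | +7 |
| 7 v 7 | 37 | 37 | 0 |
| 3 v 7 | 33 | 37 | −4 |
| 21 v 1 | 51 | 31 | +20 |
| 42 v 21 (edge of major deviation) | 72 | 51 | +21 |

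A five-fraction course in both arms adds 4 days to each length and leaves the differences unchanged.

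**Length by procedure, at the permitted maxima**
- After resection, standard: gap + SRS span + 30 = 21 + 0 + 30 = 51 days, or 21 + 4 + 30 = 55 days.
- After resection, investigational: surgery comes last, so 30 days.
- After the end of SRS, standard: SRS comes last, so 30 days.
- After the end of SRS, investigational: 7 + 30 = 37 days.

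The post-resection difference needs no assumption about actual gaps: it favours longer capture in the standard arm for any gap above zero. The post-SRS difference runs the other way.

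**Size for a crude count.** This is an illustration only, assuming a constant and equal hazard and every patient at the maximum gap. If 20% have an event in 37 days, the proportion in 51 days is 1 − 0.80^(51/37) = 26.5%.

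**The case against.** The strongest objection is that no named endpoint compares all-cause adverse event counts. The safety endpoint is adverse radiation events, and necrosis that is recognised or suspected should pass a filter that admits possibly related events. MRI, steroid dose and neurocognitive testing are scheduled at every follow-up visit with no attribution condition. This stands, and it limits the damage to the necrosis endpoint. It does not cover new neurological symptoms that could be due to tumour, surgery or radiation. The masked review applies to imaging and pathology material and is not stated to adjudicate such events or their relatedness.

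A second objection is that the comparison window is an analysis choice, properly left to the analysis plan. That is partly right: exposure-adjusted rates or a shorter common window could be specified there. But Table 5 is a collection rule, and no analysis can recover events that were never recorded. Truncation also costs information. Cutting both arms at 37 days from first treatment leaves a standard-arm patient irradiated on day 21 with 37 − 21 = 16 days observed after SRS.

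A reader might go further and infer that the standard arm always has about two weeks more all-cause capture, that equal event rates would therefore appear as a count ratio of 69/55 = 1.25, and that the bias always favours preoperative SRS. The documents do not support this:
- Both the two weeks and the ratio compare upper limits, and other permitted gaps give a smaller, zero or negative difference.
- After SRS the longer window belongs to the investigational arm.
- The sentence introducing Table 5 limits it to events secondary to radiotherapy, so the all-cause reading rests on the unconditional entries in the table's first row. If the sentence governs instead, attribution by an unblinded investigator applies from consent onwards.

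**Conclusion.** The point holds in a limited form. Unconditional recording ends on a date that depends on the arm, with a permitted-maximum difference of 14 days (day 69 v day 55, assuming treatment starts on day 14 and takes five fractions). The realised difference depends on gaps that the document does not fix.

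The direction depends on the event. Capture after resection is longer in the standard arm (up to 51 to 55 days v 30), and capture after SRS can be longer in the investigational arm (up to 37 days v 30). Crude adverse event counts are therefore not comparable between arms, above all for post-surgical events.

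After the cut-off, differential recording of ambiguous neurological events is possible. The documents do not show its size or direction, and recognised necrosis should be little affected. The scope of Table 5 is stated in two ways that do not agree.

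**What to change.** 1. Record adverse events in both arms, without a relatedness condition, to a fixed number of days from randomisation, and compare them over that window. It should cover the later of the current limits. Day 90 does so, including at the edge of a major deviation in the standard arm. The 3-month visit would not serve: it is counted from the last treatment, which at the maxima is day 14 + 21 + 4 = 39 v day 14 + 4 + 7 = 25, so it carries the same 14-day difference. At those maxima, day 90 leaves at least 90 − 39 = 51 days after SRS and 90 − 25 = 65 days after resection in both arms, enough for equal procedure-specific windows.
2. At later scheduled visits, record neurological events and suspected radiation necrosis regardless of attribution, with the investigator's relatedness judgement as a separate field.
3. Reconcile Table 5 with its introductory sentence so that it is clear whether the first period covers all adverse events or only those secondary to radiotherapy.

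The cost is an edit to Table 5 and some extra adverse event entries. The adverse event review is already scheduled at every follow-up visit, so no visits are added there; events up to day 90 can be recorded at the first of these visits that follows it.
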